## Abstract

**Background:**

Type 2 diabetes is one of the fastest growing chronic diseases internationally. The health complications associated with type 2 diabetes can be prevented, delayed, or improved via early diagnosis and effective management. This research aims to examine the impact of a primarily web-based educational intervention on the diabetes care provided by general practitioners (GPs) in rural areas, and subsequent patient outcomes. A population-level approach to outcome assessment is used, via whole-town de-identified pathology records.

**Methods/design:**

The study uses a cluster randomised controlled trial with rural communities as the unit of analysis. Towns from four Australian states were selected and matched on factors including rurality, population size, proportion of the population who were Indigenous Australians, and socio-economic status. Eleven pairs of towns from two states were suitable for the trial, and one town from each pair was randomised to the experimental group. GPs in the towns allocated to the experimental group are offered an intervention package comprising education on best practice diabetes care via an on-line active learning module, a moderated discussion forum, access to targeted and specialist advice through an on-line request form, and town-based performance feedback on diabetes monitoring and outcomes. The package is offered via repeated direct mail.

**Discussion:**

The benefits of the outcomes of the trial are described along with the challenges and limitations associated with the methodology.

**Trial registration:**

Australian New Zealand Clinical Trials Registry: ACTRN12611000553976

## Background

Type 2 diabetes is one of the fastest growing chronic diseases internationally [1]. It is estimated that world prevalence of diabetes in adults will rise from 6.4% in 2010 to 7.7% by 2030 [2]. Long-term complications associated with diabetes include macrovascular disease, coronary heart disease, stroke, retinopathy, and kidney diseases [3]. Those diagnosed with diabetes have double the risk of developing cardiovascular disease (CVD) and have a higher mortality due to their first CVD event [3,4]. Diabetic nephropathy affects approximately 10% of people with diabetes, is the most common cause of end-stage kidney disease, and diabetes is a major contributor to lower limb amputations and visual loss [3]. The direct and indirect costs of diabetes and its associated complications to the health system and to individuals is substantial [5].

The health complications associated with type 2 diabetes can be prevented, delayed, or lessened if diabetes is diagnosed early and is well controlled. While there are many factors important to diabetes control, metabolic markers of poor diabetes control such as elevated blood glucose, blood lipids, cholesterol, and urinary albumin indicate increased risk of diabetic complications [6-11]. Interventions designed to impact on multiple risk factors in people with diabetes can reduce risk of diabetes complications [6,12]. However, achieving optimal diabetes management at a population-level remains challenging.

General practitioners (GPs), or primary care physicians, play a major role in diabetes management [3]. In an effort to improve diabetes management, national Clinical Practice Guidelines for general practice specify the requirements for testing of blood lipids, HbA1c, and urinary albumin [6,13]. Target levels for each of these metabolic indicators are provided, and follow-up care is recommended if results fall outside these parameters [13]. While these metabolic markers cannot assess the quality of an individual’s diabetes care, they represent key objective measures of the management of diabetes at a population level. While there were about 818,000 Australians diagnosed with diabetes in 2009 and 2010, it appears that a minority have received the recommended annual testing of metabolic markers [14].

In Australia, people living in regional, rural, and remote regions have mortality rates between 10% and 70% higher than those living in the major cities [15]. Rural and remote communities are of particular importance because rates of diabetes consultations are higher than in other areas of Australia [16]. Rates of diabetes-related hospitalisation rise with increasing remoteness of residence [3], as do death rates due to diabetes [3]. The proportion of diabetic patients meeting targets for total cholesterol, triglycerides, and blood pressure levels is also lower in rural areas compared with urban areas [17]. The role of the GP is critical in rural settings, because there may be less access to specialist services. In Australia, organisations such as the Rural Health Education Foundation run distance education programs, including internet-based programs for rural GPs; however, these have not been evaluated for effect on quality of care or patient outcomes.

Continuing medical education (CME) is a commonly employed mechanism to improve clinical practice [17]. There is growing evidence that CME approaches that involve multiple exposures to educational material over time and a variety of educational techniques are effective at improving doctors’ knowledge, attitudes, and patient outcomes [18]. Web-based CME is increasing in popularity and is of particular relevance to GPs in non-metropolitan locations where face-to-face training opportunities are less accessible. However, while some studies have examined the effect of CME on participant satisfaction [19], few have examined the effect on patient outcomes, and none at the population level.

Studies that examine the effect of provider-change strategies on patient outcomes have done so by looking at patients linked to providers who have participated in the study [20-22]. The outcomes at the patient level, therefore, do not include the patients of providers who choose not to participate, patients who are ‘missed’ or excluded by their provider, patients who do not provide consent, and providers or patients lost to follow-up. While these methodological flaws are often unavoidable, they severely limit the generalisability of the results. This project will use objective data to examine uptake and effectiveness of CME and additional intervention strategies at the population level in the rural setting. To meet this objective, the research design uses communities as the unit of analysis and administrative data sets (whole town de-identified pathology data) without the usual problems of generalisability resulting from enrolling practices and patients.

In addition to drawing on best evidence for CME [18] the intervention will be multifaceted; including an on-line Active Learning Module (ALM) attracting CME points, and strategies designed to improve adherence to guideline recommendations such as performance feedback [23,24]. Non-metropolitan GPs are likely to be receptive to the web-based aspects of our proposed approach because computer use by GPs in rural and remote areas is higher than that of GPs in metropolitan areas [16]. Rural towns also offer a greater chance of capturing the whole population than does a selected group of GPs.

### Aims and objectives

#### Objective

To test whether population-level improvements can be achieved by implementing evidence-based practice change strategies for GP care and management of diabetes in rural communities.

#### Primary aim

To test whether a rural GP-focused intervention involving Continuing Medical Education (CME), reminders and feedback can improve clinical outcomes as measured by glycaemic control.

#### Secondary aims

To examine whether the above-mentioned intervention can:

1. Improve patterns of diabetes care as measured by whether the frequency of testing for hemoglobin A1c, blood lipids and urinary albumin meets NHMRC (National Health and Medical Research Council) guidelines.

2. Improve other clinical outcomes as measured by blood lipid control and urinary albumin control.

## Method/design

### Study design

The study uses a cluster randomised controlled trial with towns as the unit of allocation and analysis. This enables the impact of the interventions to be examined at a population level and allowed the outcomes related to diabetes care for individuals to be examined regardless of whether care was sought from one or multiple GPs within their community. Randomisation by town may result in similar intervention effects even if patients change GPs within their town over the course of the study. Towns were randomised via a computer-generated stratified randomisation scheme in SAS (Statistical Analysis Software). Allocation remained concealed to all participants and all those assessing outcomes throughout the study. Because the clusters were towns, consent was not required from clusters or members of clusters. Management of the various challenges associated with this design is addressed in the discussion.

### Selection and matching of town sample

Towns were defined by postal area and matched to town names through the Australia Post website. Towns were eligible for selection if they: had an ‘Australian Remoteness Index for Areas Plus’ (ARIA+) [25] classification of 2.0 or greater; had a population of 10,000 to 30,000 people; were in the Australian states of Victoria, New South Wales (NSW), or Queensland, *i.e.*, where the two collaborating pathology companies operate with good coverage of regional and rural towns; and had five or more full-time equivalent GPs according to the Medical Directory of Australia and cross-matched with census data. This criterion was included to ensure GP and patient anonymity. This process identified a possible 43 towns.

Towns were matched in pairs within each state on the above variables, proportion of population identified as Indigenous, and socio-economic status (SES). Indigenous population was incorporated in the matching process because the prevalence of diabetes is higher among Indigenous Australians than in the general population [26]. SES using the Socio-Economic Index for Areas (SEIFA) was also included in the matching process because diabetes was two to two-and-a-half times more prevalent among those in the lowest versus the highest socioeconomic group [26]. The town matching process was as follows: Towns were sorted by total population, and pairs selected within each state which were the most similar; priority was given to average ARIA+, then total population, followed by Indigenous population (although for instances of a large difference in indigenous population between two towns, general population was of less importance), and then SEIFA, because all towns had similar SEIFA codes. Once towns had been divided into pairs (NSW = 7 pairs, Queensland = 6 pairs, Victoria = 2 pairs), they were ranked according to the ‘best’ pairs. A minimum distance of 100 km between paired towns was required to prevent contamination between experimental and control communities. An initial matching process incorporating all of the above criteria for inclusion, exclusion, matching, and contamination prevention indicated that there were 17 potentially matched pairs of towns (*i.e.*, 34 towns). The pathology laboratories operating in each of the 34 towns were verified via discussion with pathology providers and searching of the electronic yellow pages to identify any towns where the two collaborating pathology laboratories provided a low proportion of the pathology services. This excluded a further six pairs of towns, leaving 11 matched pairs of towns, all of which were in NSW and Queensland. One town from each matched pair was randomly allocated to the intervention group and the other to the control group. As indicated in the sample size section, a minimum of seven matched pairs (14 towns) will be required at follow-up. Given the possibility that pathology laboratory presence in a selected town may change over the course of the study with the result that one or more towns may become ineligible, all 11 town pairs were included in the study.

### Selection of case sample

For the two-year baseline period, the two pathology companies used the postcode of the treating doctor to identify the potential cases in each study town. The existence of at least one HbA1c test was the criterion for an individual to be identified as a potential case of diabetes. A study case was defined by having either a single HbA1c test where the result was greater than 7%, or two HbA1c tests within the study period. This approach was used to exclude those cases where a single HbA1c test had been used to screen for diabetes. This criterion may have resulted in the omission of some cases of diabetes (*i.e.*, people with diabetes who had not had an HbA1c test). However, more serious forms of bias are avoided, because neither provider consent nor patient consent was required.

### Data extraction procedure

For each case the following de-identified unit record data were extracted from pathology laboratory records: date of birth, gender, de-identified doctor code, postcode of doctor’s clinic, postcode of patient, date and value of each HbA1c test, date and value of each cholesterol test, date and value of each triglycerides test, date of each HDL cholesterol test, date and value of each LDL cholesterol test, and date of each urinary albumin test. The unit record data were extracted for three time periods: pre-test measures were taken over the 24 months prior to the intervention retrospectively; during the intervention, measures were collected prospectively; post-test measures will be taken in the 24 months following the termination of the intervention. Where both pathology companies operate in the same town, the two separate data sets will be combined to produce a single data set for each town.

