##### Frequency of blood lipid and urinary albumin testing

Clinical practice guidelines recommended that blood lipids and urinary albumin levels were tested once every 12 months as part of an annual cycle of care, with re-testing to occur within three months if the result was outside recommended levels [13]. Over each 24-month period, the number of all cases where there was at least one gap between tests of more than 12 months (13 months or greater) was determined and aggregated for each town. For each case with at least one test outside recommended target levels [13], the number of cases where a subsequent gap between tests of more than three months (four months or greater) was determined and aggregated for each town. The mean gap between blood lipid and urinary albumin tests for each case was also determined.

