##### Blood lipids and urinary albumin control

The following targets were recommended for blood lipids: total cholesterol <4.0mmol/L; triglycerides <1.5mmol/ L; HDL cholesterol >1.0 mmol/L; LDL cholesterol <2.5mmol/ L [13]. A urinary albumin excretion of <20 μg/min is considered normal [13]. Using the most recent results for each case within each 24-month timeframe, the mean values of blood lipids and urinary albumin and the proportion of all cases whose most recent values are within the relevant target ranges was determined.

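### The extraction list takes dates but no results for HDL cholesterol and urinary albumin, although control of both is a planned secondary outcome

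*Protocol article*

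**What the plan says.** The Data extraction procedure in the protocol article itemises the fields taken from the laboratory records for each case, in all three time windows. HbA1c and LDL are listed with both date and result, and so are total cholesterol and triglycerides: "date and value of each cholesterol test, date and value of each triglycerides test". HDL and urinary albumin are listed by date alone: "date of each HDL cholesterol test, date and value of each LDL cholesterol test, and date of each urinary albumin test".

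Four other parts of the article rely on results for those two markers:

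- **Secondary aims**, aim 2: "Improve other clinical outcomes as measured by blood lipid control and urinary albumin control".
- **Blood lipids and urinary albumin control** sets a target for each ("HDL cholesterol >1.0 mmol/L"; "A urinary albumin excretion of <20 μg/min is considered normal"). It defines the outcomes as the mean of the most recent values and "the proportion of all cases whose most recent values are within the relevant target ranges was determined".
- **Frequency of blood lipid and urinary albumin testing** defines a re-test measure on a subset chosen by result: "For each case with at least one test outside recommended target levels".
- **Statistical methods** commits to assessing lipid and albumin control at baseline and at post-test.

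**The concern.** A test date shows that a test was done, not what it found. A mean, a proportion within target and a subset defined by an out-of-range result all need the result itself. The field list and the outcome definitions therefore cannot both be right.

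If the list describes what the two pathology companies were asked for, part of a named secondary aim has no data behind it. The article names no other source for these results and plans no derivation of HDL from the other lipids.

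Timing matters. By the Trial status section, baseline measurement is complete and the intervention is nearly so, while the post-test extraction is still to come. A gap found now can be closed in that extraction. A gap found at analysis would have to be closed for all three windows at once, or the outcomes dropped after the data are known.

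**Working it through.** The article states no figure on this point to reproduce. The check matches what each outcome needs against what the list supplies.

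| Marker with a target | Date listed | Result listed | Mean and within-target proportion | Date-based gap measures |
|---|---|---|---|---|
| Total cholesterol | yes | yes | computable | computable |
| Triglycerides | yes | yes | computable | computable |
| LDL cholesterol | yes | yes | computable | computable |
| HDL cholesterol | yes | no | not computable | computable |
| Urinary albumin | yes | no | not computable | computable |

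1. **Control outcomes.** Five markers have a target and three have results, so 5 − 3 = 2 lack them. Each of the two loses a mean and a within-target proportion: 2 × 2 = 4 summaries per town and window. The same list applies to every town, so this holds in all 11 × 2 = 22 towns.

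2. **Secondary aim 2.** The aim has a lipid part and an albumin part. The lipid part has four targets, of which three (total cholesterol, triglycerides, LDL) remain computable and one (HDL) does not. The albumin part rests on one marker and has no results.

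3. **Conditional re-test measure.** This counts cases with a gap of four months or more after an out-of-target result. The gap needs dates, but the entry condition needs results. For albumin, no case can be placed in the subset. For lipids, cases can enter through total cholesterol, triglycerides or LDL, but not through HDL.

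4. **Gap measures.** The count of cases with a gap of 13 months or more, and the mean gap, need only dates. Both stand for all five markers.

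5. **Primary outcome.** HbA1c is listed with date and result, so the primary outcome is unaffected.

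**The case against.** The strongest counter-argument is that two words were simply left out. The section on lipid and albumin control says in the past tense that means and proportions were determined, and Trial status reports baseline as complete. Read that way, the results were held and only the list is wrong.

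This stands as a real possibility, but it does not settle the matter. The article uses the same past tense for the primary outcome across every 24-month window, including the post-test window that had not yet happened. The omission also occurs twice, on either side of LDL, which is listed in full. Dates alone would have served the testing-frequency aim, so a deliberate date-only request is plausible. The town feedback described under Intervention group reports target attainment for HbA1c and blood lipids but not for albumin. That is consistent with albumin results not being held, but does not prove it.

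A reader might infer three stronger things that the article does not support:

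- **That secondary aim 2 as a whole cannot be computed.** Three of its four lipid targets can.
- **That exactly two re-test measures are lost.** The article does not say whether lipids are handled one by one or as a panel, so the loss of a whole measure is firm only for albumin.
- **That the data are certainly missing, or will be hard to recover.** The article says nothing on how easily the companies could supply the results again.

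**Conclusion.** The contradiction between the field list and the outcome definitions is certain from the text. That data are missing is conditional on the list being literal.

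On that condition, HDL and urinary albumin have no control outcome, albumin has no conditional re-test measure, and the lipid re-test measure cannot take account of HDL. Secondary aim 2 is then partly lost: all of its albumin part and one of the four targets in its lipid part. The primary outcome, the other three lipid targets and every date-based measure are sound on either reading.

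Correction is needed either way. Either the list misdescribes the data, or the outcome sections promise results that the data cannot give.

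**What to change.** Take the steps in this order.

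1. **Check now** whether HDL and urinary albumin results were supplied by both pathology companies for the baseline and intervention windows.

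2. **If they were**, correct the Data extraction procedure so that both markers are listed with date and result. For albumin, also state the unit or type of test, because the target is expressed as an excretion rate per minute and a result in another unit could not be set against it directly. The cost is a line of text.

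3. **If they were not**, add the two result fields to the post-test extraction and re-pull the two earlier windows from the same laboratory records. Changing the post-test extraction alone would leave no baseline for the comparison in Statistical methods. The baseline was itself a retrospective pull, so a second one is feasible in principle. The cost is two more fields in an existing query and a re-run for the earlier windows, with no patient contact. Whether both companies can do this has to be confirmed with them.

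4. **If the results cannot be supplied**, make these changes before post-test data are seen:
   - remove albumin control from Secondary aims, from the control outcomes and from Statistical methods;
   - remove HDL from the control targets;
   - remove both markers from the conditional re-test measure;
   - keep the date-based frequency measures for both.

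The cut-off is the post-test data because baseline results have already been used for feedback to GPs.

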### Measures

#### Primary outcome

##### Glycaemic control

The incidence and progression of complications of diabetes are reduced for people with lower HbA1c [8-10]. Therefore, guidelines recommend an overall target of ≤7.0% for HbA1c [6]. Using the most recent HbA1c for each case within each 24-month timeframe, the mean HbA1c across the town, and the proportion of all cases whose most recent HbA1c value is ≤7.0%, was determined.

#### Secondary outcome

##### Frequency of HbA1c testing

NHMRC guidelines [6] recommended HbA1c testing every six months if the result was <7.0%, with re-testing to occur within three months if the result was ≥7.0%. Over each 24-month period, the number of all cases where there was at least one gap between tests of more than six months (seven months or greater) was determined and aggregated for each town. For each case with at least one HbA1c test >7.0%, the number of cases where a subsequent gap between HbA1c tests of more than three months (four months or greater) was determined and aggregated for each town. The mean gap between HbA1c tests for each case was also determined.

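### The three-month re-test measure is not tied to the interval after the out-of-target result, so patients who regain control and then follow the longer guideline interval can be scored as failures

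*Protocol article*

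**What the plan says.** Under Frequency of HbA1c testing, the protocol article cites a guideline whose interval depends on the last result: it "recommended HbA1c testing every six months if the result was <7.0%, with re-testing to occur within three months if the result was ≥7.0"%. The re-test measure is then set per case. It opens "For each case with at least one HbA1c test >7.0"%, and for those cases "the number of cases where a subsequent gap between HbA1c tests of more than three months (four months or greater) was determined", aggregated by town over each 24-month period.

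Frequency of blood lipid and urinary albumin testing follows the same pattern. The cited guideline is that "blood lipids and urinary albumin levels were tested once every 12 months as part of an annual cycle of care", with a three-month re-test when a result is outside the recommended level. Among cases with at least one such result, "the number of cases where a subsequent gap between tests of more than three months (four months or greater) was determined".

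Secondary aim 1 asks whether testing frequency meets the guideline. Both sections also give a general gap measure (seven months or more for HbA1c, 13 months or more for lipids and albumin) and a mean gap.

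**The concern.** The guideline attaches the three-month interval to a result; the measure attaches it to a person. Once a case has one out-of-target result, the wording lets a later gap of four months or more count, even when that gap starts at an in-target result for which the same section quotes six or 12 months.

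The patients misclassified in this way are those who regained control, which is what the primary aim seeks to bring about. The error therefore depends on the effect under test and need not cancel between arms. A difference between intervention and control towns on this measure could reflect testing behaviour, control, or both, and could not be read as guideline adherence.

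**Working it through.** The article gives no figure for this measure, so there is nothing of its own to reproduce. The sample-size calculation concerns the primary outcome and does not enter.

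**Step 1: one adherent patient, from the quoted rules alone.**
- Month 0, HbA1c 7.6%: re-test due within three months.
- Month 3, HbA1c 6.8%: re-tested on time, in target, next test due at six months.
- Month 9: tested on time.

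Both intervals comply. The second is six months long, comes after a result above 7.0%, and is at least four months. The case counts as a failure. For lipids or albumin, a correctly timed 12-month interval after a return to target does the same.

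**Step 2: share of fully adherent cases scored as failures.** Assumptions not in the documents: the first high result is uniform over months 0 to 6 of the 24-month window; re-tests come at three months while high and at six months once in target; r is the probability of returning to target at each re-test; there is no relapse. A failure needs the six-month gap to be completed by month 24. That allows a return at any of the first five re-tests if the first high result falls in months 0 to 3, and any of the first four if it falls in months 3 to 6:

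failure share = ½[1 − (1 − r)^5] + ½[1 − (1 − r)^4]

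| r | First half | Second half | Failure share |
|---|---|---|---|
| 0.05 | 22.6% | 18.5% | 20.6% |
| 0.10 | 41.0% | 34.4% | 37.7% |
| 0.20 | 67.2% | 59.0% | 63.1% |
| 0.30 | 83.2% | 76.0% | 79.6% |

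A separate simulation with half of patients starting out of target and relapse of 0.05 to 0.20 per test gives 29–34% at r = 0.10 and 49–58% at r = 0.20. A measure tied to the interval starting at each out-of-target result gives 0% throughout, as it should.

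**Step 3: imperfect adherence.** Same set-up as step 2, but a share of tests is late by one to six months (assumed). The two columns have identical testing behaviour and differ only in r.

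| Tests on time | r = 0.10 | r = 0.20 | Spurious difference |
|---|---|---|---|
| 100% | 37.7% | 63.1% | 25.4 points |
| 90% | 63.5% | 78.0% | 14.5 points |
| 70% | 89.5% | 93.3% | 3.8 points |
| 50% | 98.0% | 98.5% | 0.5 points |

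At low adherence the difference vanishes because almost every eligible case fails. The measure then discriminates poorly for a different reason.

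**Step 4: raw count per town.** Only cases with a result above 7.0% can enter, so better control also shrinks the eligible group. Take relapse of 0.10, r rising from 0.10 to 0.20, and the share starting out of target falling from 50% to 40% (all assumed). Failures as a share of all cases rise from about 20% to 28% at perfect adherence, but fall from about 54% to 46% when half of tests are on time. The direction of the count depends on rates the documents do not give.

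**The case against.** The strongest reply is about wording. The general measure speaks of at least one gap, whereas the re-test measure uses the singular for a subsequent gap, shortly after the re-test rule is quoted. The authors may have meant the gap directly after the high result, and on that reading no adherent patient is misclassified. This stands as a possibility. But the text does not say it, eligibility is defined by person rather than by result, and two programmers could reasonably code two different measures.

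The second reply is that perfect adherence is the worst case. The Background says that only a minority appear to receive the recommended annual tests, and step 3 shows how quickly the difference shrinks. This stands: the 25-point figure is an upper illustration.

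A reader might go further and infer that an effective intervention must raise the failure count, so that the measure is biased against the intervention by a known amount. The documents do not support that. Step 4 shows that the count can move either way, and the intervention also acts on testing frequency directly, which lowers failures.

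Finally, secondary aim 1 does not rest on this measure alone. The seven-month, 13-month and mean-gap measures, and the 12-month HbA1c analysis promised under Variation between guidelines on HbA1c test frequency, do not share the defect. That limits the harm but does not make this measure valid.

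**Conclusion.** The concern holds for the definition as written. On the plain reading, the measure scores guideline-adherent patients as failures and, among eligible cases with testing behaviour held fixed, does so more often as more of them return to target. It cannot serve as a measure of guideline adherence. That much follows from the quoted rules without outside figures.

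The size does not follow from the documents. For assumed return rates of 0.10 against 0.20, it runs from about 25 points at perfect adherence to under 1 point at 50% on-time testing. The change is worth making, but this is a secondary outcome and the primary outcome is untouched.

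A smaller inconsistency sits in the same section: the guideline trigger is stated as 7.0% or above, while the measure takes only results above 7.0%. A result of exactly 7.0% falls under one and not the other, and the two must be reconciled.

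**What to change.** In both testing-frequency sections, define the re-test measure on the interval that starts at each out-of-target result. Count it as met if the next test comes before four months, and report per town the proportion of out-of-target results followed by a timely re-test. Scoring by result is preferable to scoring by case. Even a correctly tied case-level measure moves with control, because cases that return to target sooner have fewer chances to fail: in the 90% scenario of step 3 it goes from 35.0% at r = 0.10 to 29.3% at r = 0.20 with the same testing behaviour. Score the baseline and post-test periods identically, including out-of-target results too close to the end of a window to be classified.

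Apply this to HbA1c, total cholesterol, triglycerides and LDL cholesterol, for which Data extraction procedure lists both dates and values. For HDL cholesterol and urinary albumin it lists dates only; confirm that values are extracted, or drop the result-dependent measure for those two. Reconcile the two 7.0% triggers in the same edit.

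The cost is a rewording of two outcome definitions and a small programming change. The four analytes with listed values need no new data, and the baseline period can be re-scored from existing records.
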